**Subtitle:**

Randomized, Double-Blind, Placebo-Controlled, Phase 1b Clinical Study to Evaluate the Activity, Pharmacokinetics, Safety and Tolerability of Celgosivir in Adults with Confirmed Dengue Fever

# Background

Globally, dengue infections result in more than 20,000 deaths, nearly 500,000 hospitalized cases and anywhere between 50-100 million human infections annually [WHO 2009]. Dengue infection is caused by one of four immunologically distinct serotypes of the dengue virus (DENV 1-4). The virus is spread by the urban-breeding mosquito *Aedes aegypti*. Usually, infection with any one of the four DENV serotypes leads to mild, self-limiting dengue fever with lifelong immunity to that specific serotype. Epidemiological evidence also indicates that 90% of the severe and potentially fatal dengue diseases, dengue hemorrhagic fever (DHF) or dengue shock syndrome (DSS) occur during secondary heterotypic infections where the protective antibody from a prior infection takes on a pathogenic role, so-called Antibody Dependent Enhancement (ADE) [Fink 2006, Halstead 2007]. The antibody response triggers a systemic inflammatory reaction resulting in vascular leakage. There is no approved preventative vaccine or antiviral treatment for dengue disease. The World Health Organization has listed dengue fever as an emerging and uncontrolled disease [Remme 2002]. In Singapore, despite expenditures by the National Environment Agency of SG$63 million per year on mosquito vector control, the average number of dengue cases from 2007 to 2010 is >6000 per year. Hence there is a need for an antiviral compound in Singapore, and even more so in other tropical countries that do not have as effective vector control as Singapore.

Celgosivir is a butyl ester derivative of castanospermine, a natural product derived from the seeds of *Castanospermum australe*. It exerts antiviral activity by inhibiting host alpha-glucosidases I and II, enzymes essential for proper folding of dengue-encoded proteins such as E, prM and NS1 [Courageot 2000, Rathore 2011]. Fluorescence microscopy images demonstrate that celgosivir inhibits production of dengue NS1 protein in infected cells [Rathore 2011]. Without glycosylated proteins, infectious viral particles accumulate in the endoplasmic reticulum (ER), and mature virions cannot be produced. Since the drug target is a host enzyme required for viral maturation, the potential for development of resistance is expected to be lower than a drug directed against a viral enzyme. Celgosivir exhibits activity against a variety of laboratory and clinical dengue strains of DENV1-4, with submicromolar EC50 values. Celgosivir has been tested in AG129 mice lacking interferon-  and  receptors, which were infected with a clinical strain of DENV-2. In this model, celgosivir significantly reduced viremia by 88% and 55%, respectively, when given at the time of infection and when treatment was delayed by a day [Schul 2007]. In a lethal model of viremia, mice were pretreated with an antibody against DENV E protein to model ADE and then infected with a mouse-adapted strain of DENV-2. In this animal model, untreated mice had 0% survival by Day 5, whereas mice treated with 50 mg/kg celgosivir PO bid, 100% were still alive at Day 12 (p = 0.0001). Even when treatment was delayed by 24 and 48 hr, celgosivir was still able to confer protection, with 75% and 50% survival, respectively to Day 12. Treatment at 10, 25, and 50 mg/kg PO bid results in 12%, 62% and 100% survival. When mice are treated once daily at 100 mg/kg PO, no mice survive past day 6 compared to 100% survival at 50 mg/kg twice daily, indicating that the drug, when divided into two doses, is more effective that giving the same total dose once a day.

Celgosivir has been evaluated in humans as a potential treatment against HIV and Hepatitis C (HCV). Marion Merrell Dow, which subsequently became Hoescht Marion Roussel, conducted the HIV program in the US and Europe in the 1990s. The US program had regulatory oversight under FDA IND 44,158, filed by Marion Merrell Dow in 1994. An IND is only granted for first-in-human studies when nonclinical toxicology performed under GLP standards indicates that the molecule has an adequate safety profile for human testing. The studies included acute studies in mice, rats and dogs, as well as repeat dose studies in rats, dogs and nonhuman primates, for up to 30 days. The main clinical and laboratory findings in a 28-day rat study were decreased body weight and food consumption, increased liver enzymes AST and ALT, and decreased platelets (only at 100 mg/kg/day). Pathological findings were intralysosomal glycogen accumulation and degeneration of hair follicles that were reversible upon discontinuation of drug. The NOAEL was <10 mg/kg/day. Dogs had a similar spectrum of toxicology findings, and in addition, experienced emesis and diarrhea in a 30-day study. The NOAEL in dogs was 5 mg/kg/day in females and between 1 and 5 mg/kg/day in males. Acute cardiovascular and CNS safety pharmacology studies had no significant findings. Genotoxicity tests (Ames, forward mutation assay, and chromosomal abberation assays) were all negative. In the early 2000s, Migenix pursued celgosivir as a treatment for HCV (another member of the *Flaviviridae* family) under regulatory oversight by Health Canada.

The human safety and tolerability of celgosivir has been tested in over 600 subjects at doses between 10 and 600 mg [Kaita 2007]. The drug has been chronically dosed with daily dosing for 12 weeks in over 340 HIV patients and 65 HCV patients. It also has been evaluated in some HCV patients for between 24 and 48 weeks at 400 mg PO daily [Durantel 2009]. Celgosivir is well absorbed with a Tmax <1 h and a half-life of 13-30 hr, with dose proportional exposure between 10 and 450 mg [Stoltz 1996, Sorbera 2005]. Celgosivir is rapidly converted to castanospermine, which is excreted unchanged in the urine, with no other metabolites detected. Adverse events were largely gastrointestinal, namely flatulence and diarrhea, of mild to moderate intensity. Asymptomatic elevations in serum creatine kinase were also observed, which were reversed within 2 weeks after discontinuation of the drug. No serious adverse events have been reported. Although celgosivir exhibited antiviral activity, it was not superior to existing treatments for HIV and HCV, and further development for those diseases was discontinued.

Celgosivir is in the class of alpha-glucosidase inhibitors. Another alpha-glucosidase I inhibitor, acarbose, is approved in the US, Europe and Singapore for treatment of Type 2 diabetes mellitus. The recommended dose of acarbose is 50 to 100 mg TID for a total daily dose of 150 to 300 mg.

In summary, the activity of celgosivir in several nonclinical *in vitro* dengue assays, reduction of viremia and significantly improved survival in animal models of dengue infection after celgosivir treatment, a record of safety and tolerability in human clinical trials for HIV and HCV up to 400 mg QD for 12 weeks, and the urgent need for dengue antiviral agent provide a compelling rationale for undertaking a proof-of-concept clinical trial of celgosivir for treatment of acute dengue fever.

Initiation of the trial will be contingent on obtaining approval of the relevant Investigational Review Board and the Health Sciences Authority of Singapore.

# Objectives and hypotheses

## Primary objectives

To investigate the effectiveness of celgosivir for treating acute dengue fever in adult patients

1. Hypothesis: The mean of virological log reduction (VLR) at Day 2, Day 3 and Day 4 will be greater for patients taking celgosivir than for those taking placebo (virological endpoint)
2. Hypothesis: The AUC above baseline of the fever curve for patients taking celgosivir will be lower than for those taking placebo (clinical endpoint)

## Secondary objectives

1. To investigate the safety and tolerability of celgosivir

Hypothesis: The proportion of patients experiencing adverse events (AEs) or serious adverse events (SAEs) will be the same or lower in patients taking celgosivir than those taking placebo.

1. To investigate the effect of celgosivir on the time to viral clearance of dengue fever patients

Hypothesis: The time of viral clearance will be shorter for patients taking celgosivir than for those taking placebo

1. To investigate the effect of celgosivir on the serum NS1 of dengue fever patients

Hypotheses:

1. The mean serum NS1 concentration between Day 2 and Day 5 inclusive will be lower for patients taking celgosivir than for those taking placebo after adjusting for primary and secondary infection
2. The time to NS1 clearance will be shorter for patients taking celgosivir than for those taking placebo
3. To investigate the effect of celgosivir on the change in leukocyte and platelet counts of dengue fever patients

Hypothesis: The maximal change from baseline in leukocyte and platelet counts from Day 2 to Day 5 will be lower in patients taking celgosivir than those taking placebo

1. To investigate the effect of celgosivir on hemoconcentration in dengue fever patients

Hypothesis: The mean maximal hemoconcentration from Day 2 to Day 5 will be lower in patients taking celgosivir than those taking placebo

1. To characterize the population pharmacokinetics (PK) of celgosivir

Hypothesis: The clearance and volume of distribution of celgosivir will be dependent on weight and independent of age and sex.

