Fifty (50) patients will be randomized 1:1 to celgosivir or placebo. Capsules of placebo or celgosivir will be administered for 5 days. Patients will be given an initial loading dose of 400 mg followed by a maintenance dose of 200 mg every 12 hr for a total of nine (9) doses. Drug should be taken 1 hr before consuming food or 2 hr afterwards. Patients will be placed on a special diet of protein, vitamins, and glucose containing minimal complex sugars or starches. Oral intake of fluids will be recorded. While in hospital from Day 1 to Day 5, daily clinical exams will be conducted, and blood samples will be collected for plasma viral load, NS1, hematology, clinical chemistry, cytokine levels and safety observations. During this period, eight serum samples will be obtained for drug levels. On Study Day 5, after blood draws, administration of the last dose, safety assessments, determination of risk for DHF or DSS, and satisfactory clinical status, the patient will be discharged. Patients at risk for or who have dengue hemorrhagic fever (DHF) or dengue shock syndrome (DSS) will remain in hospital until fit for discharge. Patients who progress to DHF or DSS may require intravenous fluids, platelet and/or blood transfusions and evaluations from other clinical specialists. At discharge, the patient will be asked to return on Study Days 7, 10, and 15 for blood sampling and safety assessments. Patients will complete visual analog scales for joint and muscle pain (VASP), and be evaluated for safety and tolerability daily while in hospital and at each subsequent outpatient visit. While in hospital, concomitant usage of analgesics will be recorded. As an outpatient, patients will keep a diary of concomitant usage of analgesics. If the patient remains in hospital past day 5, planned outpatient study assessments will be collected in hospital.

The patient will complete the study on Study Day 15 after the investigator has completed the final assessment, unless ongoing adverse events require monitoring. For subjects prematurely terminating participation in the study, assessments planned for Study Day 15 will be obtained if possible, and study completion evaluations must be performed.

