Serum or plasma samples for viremia, quantitative NS1, immunological profile, DNA and RNA analysis, and PK will be transferred to Duke-NUS, Singapore Immunology Network, National University of Singapore or other laboratories for analysis and/or storage. The period of storage will not exceed 5 years.

After all study assessments have been completed on all patients and the database is locked, unblinding will occur. The primary virological endpoint will be the mean of virological log reduction (VLR) Study Day 2 to 4 between placebo and study drug groups. The primary clinical endpoint will be a reduction in fever AUC above baseline. Secondary endpoints for antiviral activity will be time to viral clearance, serum NS1 levels, leukocyte and platelet count, and hemoconcentration.

Secondary endpoints for assessing safety and tolerability are the number and severity of all adverse events and severe adverse events related to study drug compared to placebo using the 2009 WHO classification for grading adverse drug events. In addition, eight (8) samples for celgosivir serum concentrations will be obtained for population PK analysis.

Exploratory endpoints will be concentrations of various cytokines between placebo and treated groups, and changes in RNA expression of immunomodulatory genes. The trial will also assess the validity of the VASP and concomitant usage of analgesics between placebo and treatment groups as other measures of drug activity.

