To investigate whether patients taking celgosivir will experience a lower intensity of joint and muscle pain during the study, the intensity of joint and muscle pain recorded in the “Pain Score” section during the in-hospital stay and the outpatient diary will be obtained and compared between the two groups using two-sample t-test.

Safety outcome

Safety data will be tabulated according to the standard IMU grading scales for occurrence. The proportion of AEs and SAEs among patients will be reported by cohort.

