# Safety Assessment

## Definitions

An **adverse event** (AE) is defined as any untoward medical occurrence in a patient administered a medicinal product, which does not necessarily have a causal relationship with this treatment.

A **serious adverse event** (SAE) is defined as any untoward medical occurrence that at any dose results in death, is life-threatening, requires inpatient hospitalization or prolongation of existing hospitalization, results in persistent or significant disability/incapacity or is a congenital anomaly/birth defect.

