| Viremia | + | |  |  |  | + |  |  |  | + |  |  |  | + |  |  |  | + |  |  | + |  |  |
| Quantitative NS1 | + | |  |  |  | + |  |  |  | + |  |  |  | + |  |  |  | + |  |  | + | + | + |
| Immunological Profile (Cytokines) | + | |  |  |  | + |  |  |  | + |  |  |  | + |  |  |  | + |  |  | + | + | + |
| ~~DNA~~ | ~~+~~ | |  |  |  |  |  |  |  |  |  |  |  |  |  |  |  |  |  |  |  |  |  |
| RNA | + | |  |  |  | + |  |  |  | + |  |  |  | + |  |  |  | + |  |  | + | + | + |
| PK samples - serum e | + | |  |  |  | + |  | + |  | + |  | + |  | + |  | + |  | + |  |  |  |  |  |
| PK sample - urine f | + | |  |  | + | + | + |  | + | + |  |  | + | + |  |  | + | + |  |  |  |  |  |
| Visual Analog Scale for Pain | + | |  |  |  |  |  | + |  |  |  | + |  |  |  | + |  |  |  | + | + | + | + |
| Record Fluid Administration |  | |  | + |  |  |  | + |  |  |  | + |  | + |  | + |  |  |  | + |  |  |  |
| Verify Urine production (I/O)c |  | |  | + |  |  |  | + |  |  |  | + |  | + |  | + |  |  |  | + |  |  |  |
| Record Adverse Events |  | |  | + |  |  |  | + |  |  |  | + |  |  |  | + |  |  |  | + | + | + | + |
| Record Stool Freq & Consistency & Flatulence |  | |  | + |  |  |  | + |  |  |  | + |  |  |  | + |  |  |  | + | + | + | + |
| Record Pain Medications | + | |  | + |  |  |  | + |  |  |  | + |  |  |  | + |  |  |  | + | + | + | + |
| Record Other Concomitant Meds | + | |  | + |  |  |  | + |  |  |  | + |  |  |  | + |  |  |  | + | + | + | + |

Annotations:

a Height to be performed at screening visit only

b 2 hourly temperature monitoring

c6 hourly BP, PR, O2 saturation and I/O monitoring

d Group and Cross March (GXM) to be perform if clinical indication by study investigator only

e PK samples – serum perform at (Pre-dose, 23hr(+/-1hr) , 25 hr(+/-0.5hr), 47hr(+/-1hr), 49.5hr(+/-0.5hr), 71hr(+/-1hr), 74hr(+/-1hr)and 95hr(+/-1hr))

f PK sample – urine perform at (Pre-dose, 0 – 12hr, 12hr – 24hr, 24h – 36hr, 36hr – 48hr, 48hr – 60hr, 60hr – 72hr, 72hr – 84hr, 84hr – 96hr)

g Any subject who has a platelet count drop of ≥50,000/mm3 over a 24 hour period will require FBC monitoring every 12 hr henceforth until platelet count trend reverses.

h Clinical exam will be performed twice a day (except for Study Day 5).

| Send collected samples to Duke-NUS |
| --- |
| Send PK samples to [name] @ NUS |

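### The safety hypothesis rests on the share of patients with any AE or SAE, a measure insensitive to the gastrointestinal effects the protocol itself expects

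*Protocol*

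**What the plan says.** - **Hypothesis.** Protocol section 2.2 sets the first secondary hypothesis as "The proportion of patients experiencing adverse events (AEs) or serious adverse events (SAEs) will be the same or lower in patients taking celgosivir" than on placebo. It gives no margin and names no test.
- **Analysis.** Section 6.2, under safety outcome, is descriptive: "The proportion of AEs and SAEs among patients will be reported by cohort".
- **Second wording.** The design summary in section 3.1 gives the safety endpoint as "the number and severity of all adverse events and severe adverse events related to study drug compared to placebo". That is a count and severity measure limited to related events, not a per-patient share of all events.
- **What counts as an AE.** Section 7.1 defines it as "any untoward medical occurrence in a patient administered a medicinal product, which does not necessarily have a causal relationship with this treatment". No section says how the manifestations of dengue are to be counted.
- **What the drug is expected to do.** Section 1 says of earlier trials: "Adverse events were largely gastrointestinal, namely flatulence and diarrhea, of mild to moderate intensity". Section 4.3 prescribes a special diet because gastrointestinal effects are expected.
- **Data collection.** Table 2 has a row labelled "Record Stool Freq & Consistency & Flatulence". Its first entry is after the first dose, and the pre-dose column is blank.

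**The concern.** The drug is expected to cause a specific kind of event, but the hypothesis is tested against a measure that pools every kind. A patient who has already had some other AE cannot be counted again when the drug adds diarrhea, so the pooled share moves only through patients with no other AE.

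Patients enter within 48 hours of fever onset. The protocol plans to measure pain, platelet and leukocyte change and hemoconcentration over the following days in both arms. A substantial background of events unrelated to the drug is therefore plausible, although the protocol gives no rate.

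At stake is the safety sentence in the report. The hypothesis could be declared met because other events diluted the contrast, not because the drug was well tolerated. The two wordings of the endpoint also leave it open which result answers the objective.

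**Working it through.** **The plan's own figures.** There is none for safety. Section 6.1 sizes the trial on viremia only, and its figures reproduce: the one-sided 5% t-test has 82.4% power at 14 per group for 1 log (SD 1), and 78.7% at 25 per group for 0.7 log, close to the stated 80%. The input used here is 25 patients per arm.

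**Assumptions (not in the protocol).**
- b = share of patients with at least one AE on placebo, varied over 30, 50, 80, 90 and 95%.
- d = share of patients in whom the drug causes a gastrointestinal AE, set at 40%, independent of b.
- Background gastrointestinal AE rate = 10%.

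**Step 1: any-AE share.** On celgosivir it is 1 − (1 − b)(1 − d). The difference from placebo is therefore d(1 − b). For example, at b = 0.80 the share is 1 − 0.20 × 0.60 = 0.88, a difference of 0.40 × 0.20 = 0.08.

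**Step 2: gastrointestinal AEs alone.** On celgosivir: 1 − 0.90 × 0.60 = 0.46, against 0.10. The difference is 36 points.

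**Step 3: chance that the hypothesis appears to be met despite the harm.** No test is planned, so the direct measure is the probability that the observed count on celgosivir is equal to or below that on placebo, with both counts binomial on 25 patients. Ties count as met, because the hypothesis allows equality. The last column gives the exact power of a two-sided 5% Fisher test, only to illustrate the lost contrast.

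| Measure | Placebo | Celgosivir | Difference (points) | Observed share no higher on celgosivir | Fisher power |
|---|---|---|---|---|---|
| Any AE, b = 30% | 30% | 58% | 28 | 3% | 45% |
| Any AE, b = 50% | 50% | 70% | 20 | 9% | 23% |
| Any AE, b = 80% | 80% | 88% | 8 | 28% | 6% |
| Any AE, b = 90% | 90% | 94% | 4 | 40% | 1% |
| Any AE, b = 95% | 95% | 97% | 2 | 52% | <1% |
| Gastrointestinal AE only | 10% | 46% | 36 | 0.2% | 75% |

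**Step 4: other assumed rates.** Take diarrhea in 20% on placebo and 60% on celgosivir, and let b now be the share with an AE other than diarrhea. Fisher power on diarrhea directly is 79%. On any AE it is 45, 23, 11, 5 and 1% at b = 30, 50, 70, 80 and 90%. The pattern does not depend on the particular rates chosen.

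**Step 5: adding SAEs changes nothing.** Under section 7.1 every SAE is also an AE, so the share with an AE or an SAE equals the share with an AE.

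**The case against.** **Diarrhea is well covered elsewhere.** Section 5.1 records stool frequency and consistency for every patient, and Table 2 adds flatulence. Section 5.4 places stool data in the safety assessments and names diarrhea and flatulence among the events monitored, with unblinded DSMB review. Section 5.6 has criteria on grade 3 diarrhoea. This stands. A reader might infer that a gastrointestinal excess would go undetected, and the documents do not support that. It does not rescue the section 2.2 measure, though. The section 5.6 criteria concern grade 3, whereas section 1 describes mild to moderate events. The one scheduled interim safety review comes at 12 patients.

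**The background rate is assumed.** This also stands. Nausea and rash are optional entry criteria, not forecasts for later days, and a symptom that began before dosing need not count as an on-drug event. At 30 to 50% background the chance of an apparently met hypothesis is only 3 to 9%. That dengue gives most patients an AE is an inference, not a statement of the protocol.

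**No safety test is planned, and AE tables belong in the SAP.** The power figures are indeed illustrative only. But the hypothesis and its measure are fixed in the protocol, and two sections of it disagree, so the point is more than missing SAP detail.

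**Onset.** A reader might infer from the blank pre-dose column that on-drug events cannot be told from those present at entry. Section 7.2 records the date and time of start and end of each AE, so that does not follow. A blank pre-dose AE row also fits the definition in section 7.1. What remains is narrower: exclusion criterion 13 removes only diarrhea of grade 2 or higher, so a milder change may be present at entry with no scheduled stool or flatulence entry to compare against.

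**SAEs.** Section 7.1 includes an event that "requires inpatient hospitalization or prolongation of existing hospitalization", and section 3.1 says "Patients at risk for or who have dengue hemorrhagic fever (DHF) or dengue shock syndrome (DSS) will remain in hospital until fit for discharge". A reader might infer that the SAE share saturates as well. That is not shown: an SAE must first be an untoward occurrence, no rate of longer stays is given, and clinical signs of severe dengue are excluded at entry.

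**Conclusion.** The point holds in a limited form. The section 2.2 hypothesis, as reported under section 6.2, is insensitive to the gastrointestinal effects the protocol expects, and it differs from the endpoint in section 3.1. With an assumed 40% drug-caused rate, a 36-point gastrointestinal excess shrinks to 2 to 8 points on any AE at backgrounds of 80 to 95%, with a 28 to 52% chance that the hypothesis looks met. At backgrounds of 30 to 50% the difference is 20 to 28 points and the chance 3 to 9%.

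These figures rest on assumed rates and on independence of drug and background events. If drug-caused events fell mostly on patients who already had another AE, dilution would be greater; if mostly on patients without one, less. What is at risk is the conclusion drawn from this hypothesis, not the detection of diarrhea. It is a matter of wording and choice of measure, not an arithmetical error.

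**What to change.** 1. Reconcile sections 2.2, 3.1 and 6.2 so that one safety measure answers the objective.
2. Restate the hypothesis on events that are new, or worse in grade, after the first dose.
3. Report by arm the predicted gastrointestinal AEs and the highest grade per patient, each with the difference and its confidence interval.
4. Keep the any-AE share as a descriptive line.
5. Add a pre-dose entry for stool frequency, consistency and flatulence to Table 2.

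The cost is protocol wording, slightly more tabulation and one extra CRF entry, taken by staff who already screen for diarrhea. No patients or samples are added.
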